## Reporting of SUSARs

A SUSAR needs to be reported to EKNZ (via [name]. med. [name], Sponsor-Investigator) via BASEC and to Swissmedic for category B within 7 days, if the event is fatal, or within 15 days (all other events).

[name]. med. [name], the Sponsor-Investigator, must inform all Investigators participating in the clinical study of the occurrence of a SUSAR.

## Reporting of Safety Signals

All suspected new risks and relevant new aspects of known adverse reactions that require safety-related measures, i.e. so-called safety signals, must be reported to [name]. med. [name], the Sponsor-Investigator, within 24 hours. [name]. med. [name] must report the safety signals within 7 days to the EKNZ (local event via local Investigator) via BASEC and to Swissmedic in case of a category B study.

[name]. med. [name], the Sponsor-Investigator must immediately inform all participating Investigators about all safety signals.

## Reporting and Handling of Pregnancies

The evidence to date regarding corticosteroid exposure in pregnancy and select pregnancy and birth outcomes is limited and inconsistent (41). The evidence to date suggests that first trimester corticosteroid use may confer a small increase in the odds of cleft lip in foetuses, with or without cleft palate. However, data are conflicting and it is unknown to what extent the underlying maternal disease may contribute. There is little support that systemic corticosteroid use in pregnancy independently causes increases in risks of preterm birth, low birth weight, or preeclampsia. There is not sufficient evidence to determine whether corticosteroids could contribute to gestational diabetes mellitus. This evidence is particularly true for long-term application of corticosteroid in pregnancy (>4 weeks) (41).

In the present study corticosteroids are given for 5 days (short-term). According to Embryotox, an internet-based register on pharmaco-vigilance and embryo-toxicology (University of Charité, Berlin, Germany) the 'Planning a therapy or planning a pregnancy during treatment' may also take place 'during pregnancy for a specific systemic or local treatment with prednisone. If therapeutically possible, the maintenance dose should not exceed 10 mg / day between week eight and eleven. Emergency treatment and therapy for acute disease exacerbation are not subject to any dose restrictions'. (German original text: «Planung einer Therapie oder Planung einer Schwangerschaft unter Therapie» darf «eine indizierte systemische oder lokale Behandlung mit Prednison auch in der Schwangerschaft erfolgen. Wenn es therapeutisch möglich ist, sollte die Erhaltungsdosis zwischen Woche acht und elf möglichst 10 mg/Tag nicht überschreiten. Notfallbehandlungen und die Therapie einer akuten Krankheitsexazerbation unterliegen keinen Dosisbeschränkungen.» (<https://www.embryotox.de/arzneimittel/details/prednison/>).

GPs will screen all female participants of reproductive age (postmenarche to menopause) using a battery of questions and will exclude all females who are pregnant, plan or are actively trying to get pregnant or women who are potentially pregnant. Women with anamnestic risk of pregnancy shall not be included in this study (unprotected sexual intercourse in the last two weeks). Pregnant participants must immediately be withdrawn from the clinical study. If a participant gets pregnant during follow-up, the course and the outcome of the pregnancy should be followed up carefully by GPs, documented and reported. Any pregnancy during the treatment phase of the study and within 30 days after discontinuation of study medication will be reported to [name]. med. [name] (Sponsor-Investigator) within 24 hours. The course and outcome of the pregnancy should be followed up carefully, and any abnormal outcome regarding the mother or the child should be documented and reported.

## Periodic reporting of safety

An annual safety report is submitted once a year via [name]. med [name] (Sponsor-Investigator) to the local EKNZ and to Swissmedic in case of a category B.

The annual safety report contains information from all participating GP practices. The Sponsor-Investigator prepares it, and then submits it to the ethics committee.

### **10.1.3 Follow up of (Serious) Adverse Events**

Every possible step will be taken to ensure that all AEs of interest or SAEs are identified and documented. GPs are asked to follow-up all patients with suspected AEs of interest or SAEs and to inform the study Sponsor, [name]. med. [name]. Given the short duration of the treatment with the trial drug, it is expected that the incidence of AEs or SAEs is reasonably small. Please see more information in section 10.1 Drug studies.

## 11. STATISTICAL METHODS

### 11.1 Hypothesis

Null hypothesis:

A 5-day treatment with 40 mg (2 tablets of 20 mg) oral prednisone once daily for patients consulting a GP due to post-infectious cough after an URTI (3 to 8 weeks) will be superior to placebo and improve cough-related QoL after 14 days after randomisation (more than the minimally clinical important difference (MCID) of 1.3 of the Leicester QoL score).

Alternative hypothesis:

A 5-day treatment with 40 mg (2 tablets of 20 mg) oral prednisone once daily for patients consulting a GP due to post-infectious cough after an URTI (3 to 8 weeks) will significantly change cough-related QoL after 14 days after randomisation compared to patients who only got placebo.

### 11.2 Determination of Sample Size

Sample size was estimated to have 80% power to detect the minimal clinically important difference (MCID) set at 1.3 points (14).

To be able to detect an MCID of 1.3 points with a power of 80%, a total of N=204 patients need to be recruited for both arms. This was calculated without considering intra-patient correlation (IPC) correlation  $\rho$  ( $\rho$ ) between baseline and follow-up and without potential intra-cluster correlation (ICC) of patients treated by the same physician. To further increase power, we ignored  $\rho$  by calculating the sample size for a two-sample t-test with a two-sided alpha threshold of 5%. Sample size estimation was based on the assumption that individual LCQ scores are normally distributed. Chung et al. reported a standard deviation (SD) of 3.3 points (24). A recent trial with a design and study population similar to ours (15) reported a SD of 2.9.

We decided to use the more conservative assumption of 3.3 points. Due to the fact that the number of recruited patients per GP is limited to 10, ICC might remain small.

We expect a drop-out rate of 10%, similar to that in the abovementioned recent trial (15).

A less conservative choice of an SD of 2.9 and a  $\rho$  of 0.4, with the other parameters remaining the same, would have required a sample size of N=120. Hence, we assume that by the conservative choice of SD and by neglecting  $\rho$ , our calculation will sufficiently compensate for loss of power due to ICC and drop-outs. To compute the t-test, the current version of the R language and environment ([www.r-project.org](http://www.r-project.org)) function “power.t.test” of the stats package was applied.

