| Statistical Considerations: | 
Sample size was estimated to detect the minimal clinically important difference (MCID) of 1.3 points. A standard deviation of 3.3 points was chosen and the sample size was calculated for a two-sample t-test with a two-sided alpha threshold of 5%. Overall, to be able to detect an MCID of 1.3 points with a power of 80%, a total of N=204 patients need to be recruited. We expect a drop-out rate of 5-10% (14, 15).
 
Analysis of the primary outcome will follow the intention-to-treat principle (ITT). It will be based on the full analysis set (FAS) which includes all patients who were randomly allocated to one of the study arms. We will test if there is a statistically significant difference of the LCQ score between the intervention and control group on alpha level of 5%.
 
Analysis of secondary outcomes will be of exploratory nature and results will be interpreted for hypothesis generation. For safety analyses, total number and percentages for incidence rate of re-consultations at GP and/or hospitalisations within 3 months following randomisation will be calculated. Total AE and SAE stratified by WHO-UMC (16) causality categories within 3 months after randomisation will be presented as well. Missing data will be imputed for variables required to test the hypothesis. We assume that for patients who will complete the study only a few data will be missing (17). The reason for the missing data and whether it might be at-random or not, will be examined according to guidelines (18).
 |

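### The comparison sample size of 120 in section 11.2 should be about 134, so the drop-out reserve is smaller than stated and depends on the SD and rho

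*Protocol*

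**What the plan says.** Section 11.2 sets the target as follows: "To be able to detect an MCID of 1.3 points with a power of 80%, a total of N=204 patients need to be recruited". The test is a "two-sample t-test with a two-sided alpha threshold of 5" per cent. Correlation between baseline and follow-up (rho) and clustering of patients by physician (ICC) are left out. Two SDs are reported, 3.3 from a textbook source and 2.9 from a recent trial of similar design and population, and the larger is taken: "We decided to use the more conservative assumption of 3.3 points".

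The section then expects 10% drop-out, without inflating N. In place of inflation it offers a comparison: with SD 2.9 and rho 0.4, "with the other parameters remaining the same, would have required a sample size of N=120". From this it infers that, through the cautious SD and the neglected rho, "our calculation will sufficiently compensate for loss of power due to ICC and drop-outs".

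The synopsis (Statistical Considerations) repeats "with a power of 80%, a total of N=204 patients need to be recruited" and puts a 5-10% drop-out rate in the next sentence, without the compensation argument. Section 11.4.2 names the primary analysis as ANCOVA with baseline LCQ among the covariates. Section 11.5 provides for multiple imputation if data are judged missing at random or completely at random.

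**The concern.** Drop-out and clustering are not in the calculation. They are said to be covered by the distance between 204 and the number needed in a milder scenario. The size of that distance therefore matters, and the printed comparison number does not follow from the inputs printed beside it. A reader who tries to reproduce it will fail, and will not know whether N or rho is misprinted.

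The synopsis adds a second difficulty. Read alone, it suggests that 204 recruited, 80% power and 5-10% drop-out hold together under the stated t-test. They do not. What is at stake is how much reserve the trial has and on which assumptions, not whether 204 was a reasonable choice.

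**Working it through.** **Inputs.** Section 11.2: difference 1.3; two-sided alpha 5%; power 80%; SD 3.3 (main) and 2.9 (alternative); rho 0.4 (alternative); drop-out 10%. Synopsis and section 11.5: drop-out 5-10%. Synopsis: 102 per arm. Section 11.4.2: ANCOVA with baseline LCQ.

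**Formulas.** Normal approximation per arm: n = 2 × [SD × (1.960 + 0.842) / 1.3]². The exact figures use the noncentral t distribution, which is what R's `power.t.test` does. Adjustment for baseline multiplies the variance by (1 − rho²), so the SD is multiplied by √(1 − rho²) and n by about (1 − rho²).

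**1. The main figure reproduces.** SD 3.3: the normal approximation gives 101.2, so 102 per arm and N=204. Exact t gives 102.1 per arm, and 102 per arm has 79.95% power. This number assumes that every recruited patient is analysed.

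**2. The comparison figure does not.** SD 2.9 without rho needs 79.1 per arm by exact t. With rho 0.4, 1 − 0.16 = 0.84, the SD becomes 2.9 × √0.84 = 2.658, and 66.6 per arm are needed: 67 per arm, N=134 (132 by normal approximation).

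Other ways of using rho 0.4 at SD 2.9:

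| Approach | N |
|---|---|
| rho ignored | 160 |
| change score, factor 2(1 − rho) | 190 |
| ANCOVA, factor 1 − rho² | 134 |
| factor (1 + rho)/2 | 112 |
| factor 1 − rho | 96 |
| ANCOVA, one-sided 5% | 104 |

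None gives 120. ANCOVA with rho 0.5 (factor 0.75) needs 59.6 per arm, which is exactly N=120; solving for rho gives 0.494. At rho 0.4, 60 per arm has 75.7% power.

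**3. Effect of drop-out.** 102 × 0.90 = 91.8 per arm (about 184 in total); 102 × 0.95 = 96.9 per arm. Under the stated t-test at SD 3.3, power is 75.6% and 77.9% respectively.

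Power with 10% lost (91.8 per arm), before any ICC effect:

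| rho | SD 3.3 | SD 2.9 |
|---|---|---|
| 0 (plain t-test) | 75.6% | 85.6% |
| 0.2 | 77.3% | 86.9% |
| 0.3 | 79.5% | 88.6% |
| 0.4 | 82.6% | 90.9% |
| 0.5 | 86.6% | 93.7% |

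Break-even points with 184 analysed: a plain t-test keeps 80% for any SD up to about 3.13; at SD 3.3, ANCOVA keeps 80% from rho of about 0.32 upwards.

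**4. ICC.** The protocol gives no value. As an assumption only: ICC 0.01 to 0.05 with 4.4 (204/46 practices) to 10 patients per practice, and a full design effect 1 + (m − 1) × ICC. At rho 0.4 and 10% drop-out this gives 67.0% to 81.3% at SD 3.3 and 78.0% to 90.0% at SD 2.9. The range is pessimistic, because patients are randomised individually and not by practice.

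**The case against.** The best defence is that section 11.2 never claims the plain t-test keeps 80% after drop-out. It says openly that drop-out is outside the calculation and is offset by two things: a cautious SD and an ignored rho. The SD alone can do the work. At 2.9, the value from the trial the protocol calls similar, a plain t-test with 184 analysed has 85.6% power and needs only 160 patients. Correcting 120 to 134 still leaves the comparison number well below 184. This stands: the error shrinks the reserve and does not overturn the drop-out argument.

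Two further points also stand. The planned test is ANCOVA, so 75.6% is not its power. And 184 analysed is the unfavourable case: the primary outcome falls at day 14 while follow-up runs to 3 months, so some drop-outs may come after the primary assessment, and section 11.5 allows imputation. Imputation recovers only what the observed data predict, however, and the protocol quantifies no gain from it.

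A reader might infer that the trial is underpowered, or that recruitment should rise to 227 (204/0.9). The documents do not support that. It would require SD 3.3, no benefit from baseline adjustment and every drop-out lost before day 14, all at once.

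What the defence does not rescue is the printed number, or an assurance that covers drop-out and ICC together when ICC has no value and rho 0.4 has no source in the section.

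**Conclusion.** N=120 is wrong for the inputs printed with it. The figure is about 134, or else rho should read about 0.5. The 80% power at N=204 is a figure before drop-out under the stated t-test; with 10% lacking the day-14 outcome that test has 75.6%, with 5% it has 77.9%.

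The reserve exists but is conditional. With 184 analysed and no ICC effect, 80% is kept if the SD is at most about 3.13 or, at SD 3.3, if rho is at least about 0.32. At SD 3.3 and rho 0.4 only 2.6 points remain above 80% to absorb an ICC that is not quantified. These results assume equal arms, normally distributed scores (as section 11.2 does), gain from the baseline LCQ only, and drop-outs contributing nothing at day 14. The sample size need not change. The justification should.

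**What to change.** Keep N=204. In section 11.2:

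- Replace N=120 by N=134, or restate rho as 0.5 if that was the value used.
- Replace the statement that "our calculation will sufficiently compensate for loss of power due to ICC and drop-outs" by conditional wording, for example:

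> With 10% drop-out (184 analysed) and before any ICC effect, power is 75.6% for the unadjusted t-test at SD 3.3, 82.6% for ANCOVA at SD 3.3 and rho 0.4, 85.6% for the unadjusted t-test at SD 2.9, and 90.9% for ANCOVA at SD 2.9 and rho 0.4. Power of 80% is kept if the SD is at most about 3.13 or, at SD 3.3, if rho is at least about 0.32. Any ICC effect would lower these figures.

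In the synopsis, add that 80% at N=204 is the power under the t-test before drop-out.

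The cost is a text change. No extra patients are needed and the analysis stays as planned. The downside is that the stated power looks slightly less favourable.

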### 11.3 Statistical criteria of termination of trial

None. No interim analyses are planned.

### 11.4 Planned Analyses

Detailed description of analyses will be defined in a statistical analysis plan (SAP) before unblinding the trial. The SAP will follow the ICH E9 Guideline Statistical Principles for Clinical Trials (33). Changes to the SAP will be under version control at the CTU, University Hospital Basel. The full study protocol will be published in a peer-reviewed journal under open access (e.g. Trials).

Data will be analyzed using R.

#### 11.4.1 Datasets to be analysed, analysis populations

The full analysis set (FAS) will contain all patients who were randomly allocated to one of the trial arms. The per-protocol-set (PPS) will include all patients with full i) adherence to the allocated 5-day treatments (took all doses as defined by the study protocol) and ii) complete primary outcome and LCQ (11) score at baseline. We will consider adjustments for time-varying post-randomization confounding (34).

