## 8.3 Dose modifications

Due to the short intervention of 5 days, treatment modifications are not anticipated. However, treatment modifications are planned in the (unlikely) occasion of AE (e.g. allergic reactions to the study drug, psychotic, or pre-psychotic episode) or occurrence of SAE (e.g. sepsis, venous thromboembolism, fracture) (27) or other urgent reasons (pregnancy, cancer diagnosis, infection other than URTI). In any of those cases the treatment will be stopped immediately.

Treatment will also be discontinued when study participants withdraw their informed consent.

Treating doctors can change to open-label treatment and adjust treatment if they deem necessary for the benefit of the patients, such as in cases when the patients' clinical condition is worsening or the patient presents to the GP for consultation before the 5-day treatment is over. Throughout the trial, participants' treatment can be re-evaluated by their GPs based on clinical needs and GPs independently decide about additional treatment options. Please also see 7.4 Criteria for withdrawal/ discontinuation of participants.

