## 8.4 Compliance with study intervention

Oral and written instructions on how the medication should be taken will be provided to the study participants. Participants are required to return empty medication glass jars to their GPs as soon as this is convenient for them (e.g. on the occasion of the next consultation). Participants will be asked by the research staff/ study nurse about their medication intake at the first phone call on day 7. In the event of a missed dose, patients are instructed to continue medication intake on the next day.

GPs will inform the patient in depth on the importance to adhere to the 5-day medication intake to ensure effectiveness of the treatment. The GPs will also remind patients on the importance for the trial conduct to be available for the follow-up phone calls. Furthermore, the dosing schedule is very convenient for the participant as the medication needs to be taken only once a day during breakfast and for a clearly defined and limited timeframe (5 days). Experienced and trained research staff/study nurses will call patients by phone on day 7, 14, 28 and at 3 months to complete the LCQ and to answer questions about other outcomes, in particular about medication intake (only on day 7), possible re-consultations with their GP, possible hospitalisation and the occurrence of AE or even SAE.

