## 8.6 Trial specific preventive measures

Any co-treatment or co-medication (i.e. antitussives, inhalation, herbal teas, and homeopathic pharmaceuticals) is permitted except for the use of corticosteroids. The use of any other medical intervention by study participants will be recorded in electronic Case Report Forms (eCRF) to analyse potential influence on outcomes.

GPs will screen all female participants of reproductive age (postmenarche to menopause) using a battery of questions and will exclude all females who are pregnant, plan or are actively trying to get pregnant or women who are potentially pregnant. GPs will advise participants that they need to use contraceptives for the duration of the study and that they should inform the GP or the study team in case they suspect they have become pregnant. Women with anamnestic risk of a pregnancy shall be excluded from this study. If a participant gets pregnant during follow-up, course and outcome of the pregnancy should be followed up carefully by GPs, documented and reported. Please see section 10.1.2 for additional information on handling risk of pregnancy for this study.

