#### 11.4.2 Primary Analysis

Analysis of the primary objective will follow the intention-to-treat (ITT) principle. It will be based on the full analysis set (FAS). FAS will include all patients who gave informed consent. Patient data will be analysed according to their treatment allocation.

We will test if there is a difference of the LCQ score between the intervention and control group 14 days after randomization. A treatment effect of 1.3 points increase will be considered as MCID.

The hypothesis will be tested using analysis of covariance (ANCOVA). We will report the treatment effect with 95% confidence intervals (CI). Covariates of the ANCOVA model will be baseline LCQ scores, duration of cough, age, sex, and smoking status. Patients are considered as smokers, when they answer that they had smoked “more than 100 cigarettes in their life”, they smoke “daily” or “sometimes” to the participant survey (29).

Baseline characteristics of patients in the FAS will be presented stratified by group and summarized in a table.

To assess the robustness of our primary analysis, the following sensitivity analyses will be performed:

- Analysis of the primary outcome without imputing data (complete case analysis)
- Analysis of the primary outcome using the per-protocol data set (PPS) which is defined above
- Exploring interactions between covariates of the ANCOVA model of the primary analysis
- Exploring how the effect of the intervention varies among GP practices. For this, a linear mixed-model with treatment group as a fixed-effect and GP practices as a random effect will be fit.

We will conduct one subgroup analysis, comparing effects on the primary outcome in current smokers vs. current non-smokers. Subgroup effects will be analyzed by interaction tests and interpreted fully exploratory. We expect that effects are more pronounced in non-smokers according to reports by Ponsioen et al. (20).

Statistical analysis will be performed by the CTU of the University Hospital Basel using R language and environment ([www.r-project.org](http://www.r-project.org)).

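### The per-protocol set has no condition on non-study corticosteroids, so it keeps patients who used the one co-medication class that section 8.6 does not permit

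*Protocol*

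**What the plan says.** Protocol section 11.4.1 gives the PPS two conditions. The first is full adherence to the allocated 5-day course, explained as the patient having done so if they "took all doses as defined by the study protocol". The second is "complete primary outcome and LCQ (11) score at baseline". Section 11.4.2 uses this set as one of four sensitivity analyses meant to show that the primary result is robust: "Analysis of the primary outcome using the per-protocol data set (PPS) which is defined above".

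Two sections bear on non-study corticosteroids:

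- Section 8.6: any co-treatment or co-medication "is permitted except for the use of corticosteroids". Other medical interventions "will be recorded in electronic Case Report Forms (eCRF) to analyse potential influence on outcomes".
- Section 8.3: "Treating doctors can change to open-label treatment and adjust treatment if they deem necessary for the benefit of the patients". The same section leaves decisions on additional treatment to the GPs throughout the trial.

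The schedule in section 9.1 records concomitant treatments at randomisation and at every follow-up call. Sections 9.3.2 and 9.3.3 confirm that the day-7 and day-14 calls ask about concomitant therapy together with the LCQ.

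**The concern.** A per-protocol analysis is read as the effect among patients treated as the protocol intends. Here the set checks only that the study tablets were taken. It does not check whether the patient also took the drug class under test from another source.

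The route is plausible on the protocol's own account. Section 2.2 describes prednisone as widely prescribed for this cough, and section 8.3 leaves GPs free to add treatment. A placebo patient who completes the ten tablets and then receives a corticosteroid before the day-14 assessment has had the active drug class, yet counts as per-protocol placebo. Such use pulls the two arms together. A PPS result close to the intention-to-treat result could then be taken as reassurance on a question that the set was never built to answer.

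**Working it through.** **1. The definition against the rule.** The words about the study protocol in the first PPS condition qualify the doses of study medication. They do not bring in the co-medication rule of section 8.6. The second condition concerns completeness of data. Going through the cases:

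| Patient | Outcome under 11.4.1 |
|---|---|
| Switched to open-label treatment before finishing the tablets | Fails the first condition, excluded |
| Finished the tablets, no other corticosteroid, both LCQs complete | Included |
| Finished the tablets, non-study corticosteroid before the day-14 LCQ, both LCQs complete | Included |

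The third row is the gap. It consists mainly of patients who start a corticosteroid after the course ends on day 5 and before the day-14 LCQ.

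**2. The plan's own figure.** Inputs from section 11.2: difference 1.3, SD 3.3, two-sided alpha 5%, power 80%, 1:1 allocation.

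n per arm = 2 × (1.96 + 0.8416)² × 3.3² / 1.3² = 2 × 7.849 × 10.89 / 1.69 = 101.15, rounded up to 102, so N = 204.

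This reproduces the stated sample size. The exact t-test gives 102.12 per arm, and its power at 102 per arm is 0.80. Nothing in this point disturbs that figure. It supplies the 1.3 and the 3.3 used below.

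**3. Illustration of size.** Let c be the share of placebo patients in the PPS who used a non-study corticosteroid. The protocol gives no value for c. Assume that the drug has the full 1.3-point effect in those patients and that extra corticosteroid adds nothing in the prednisone arm.

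Apparent difference = 1.3 × (1 − c)

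- c = 5%: 1.3 × 0.95 = 1.235, or 1.24
- c = 10%: 1.3 × 0.90 = 1.17

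Power of a two-sample t-test with SD 3.3:

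| c | Apparent difference | 102 per arm | 90% retained in PPS |
|---|---|---|---|
| 0 | 1.30 | 0.80 | 0.76 |
| 5% | 1.24 | 0.76 | 0.71 |
| 10% | 1.17 | 0.71 | 0.67 |

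A corticosteroid started shortly before day 14, or only partly effective, would dilute less, so for a given c these are upper limits on the dilution.

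**4. What excluding the users could do.** Suppose, as an extreme case, that the users are the 10% of placebo patients with the worst day-7 LCQ, and that day-7 and day-14 scores correlate at 0.3 to 0.8 (assumed). Removing the lowest 10% of a normal distribution raises the mean of the rest by 0.1755 / 0.90 = 0.195 SD on day 7. On day 14 this is 0.195 × 3.3 × 0.3 = 0.19 to 0.195 × 3.3 × 0.8 = 0.51 points. The contrast would become 1.3 − 0.19 = 1.11 down to 1.3 − 0.51 = 0.79. In that case the exclusion distorts more than the dilution to 1.17 that it removes, so neither version of the set can stand alone.

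**The case against.** The strongest objection is about consequence. The PPS is one of four sensitivity analyses, the trial is a superiority trial, and the primary analysis follows intention to treat. Dilution moves the estimate towards no difference and does not create a false positive. Co-medication is recorded with the stated aim of analysing its influence on outcomes, and the set can still be refined before unblinding. All of this stands and limits the weight of the point. It does not remove it: section 11.4.1 states the definition in full and section 11.4.2 relies on it as stated, so this is a stated rule with a gap and not a detail left open for the SAP.

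A second objection is that section 8.3 may make added corticosteroids an allowed clinical decision, so that they would not be a deviation at all. Sections 8.3 and 8.6 do not settle this between them. That is a reason to reconcile them, and it is why both versions of the PPS result are needed.

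A third objection is that excluding users selects on behaviour after randomisation. This also stands, as the last step of the working shows.

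A reader might go further and infer that the PPS carries all the corticosteroid contamination of the intention-to-treat analysis. It does not: patients switched before finishing the tablets already fail the first condition.

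A reader might also infer that the time-varying adjustment mentioned in section 11.4.1 is impossible because adherence is asked only once, on day 7. The documents do not support this. The section says only that such adjustment will be considered. One recall question on day 7 can cover a course that ended on day 5. No section plans to put the day-7 LCQ into the model as a covariate.

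**Conclusion.** The point holds in a limited form. As defined in section 11.4.1, the PPS keeps patients who complete the study tablets and also use a non-study corticosteroid before the day-14 LCQ, the only class that section 8.6 does not permit. The analysis therefore does not show the effect of protocol-conform treatment.

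The size cannot be derived from the protocol. Under assumed use in 5% to 10% of placebo PPS patients, full effect in those patients and no added effect in the prednisone arm, 1.3 points would appear as 1.24 to 1.17. The loss is modest and confined to a sensitivity analysis. The primary intention-to-treat analysis and the sample size of 204 are not affected. The point is worth acting on because the remedy is cheap and the data are already being collected.

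**What to change.** Add a third condition to the PPS in section 11.4.1: no oral or inhaled corticosteroid other than study medication between randomisation and the date of the day-14 LCQ, as reported in the concomitant-treatment questions at the day-7 and day-14 calls. Report the PPS result with and without this exclusion, give the number excluded per arm, and state that the exclusion selects on post-randomisation behaviour because users may be the patients with the worst cough.

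Reconcile sections 8.3 and 8.6 so that it is clear whether use of non-study corticosteroids counts as a protocol deviation. Which way that is resolved is for the sponsor.

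The cost is a few sentences in the protocol and SAP before unblinding and one additional run of a model already planned, with no new data collection. The restricted set loses some patients: at 5% to 10% use among 102 placebo patients, about 5 to 10 (102 × 0.05 = 5.1; 102 × 0.10 = 10.2), plus any users in the prednisone arm.
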